### Safety

2.8

A safety monitoring board composed of three independent experts on mechanical ventilation who do not participate in the conduct of the trial will supervise the safety of the study.

On the basis of clinical experience and the results of physiologic studies (18–20), the additional risks for patients enrolled in the PMI-targeted group are expected to be minimal in comparison to the standard of care employed in the VT/RR-targeted group. Nonetheless, patient insurance will be granted to cover all unexpected adverse events caused by the trial interventions. All adverse events will be monitored and reported to the safety monitoring board. The board will review and examine the report and provide written recommendations to the chief investigators.

### Sample size and statistical analysis

2.9

#### Sample size estimation

2.9.1

Our previous studies showed that the mean (± standard deviation) VFDs in Chinese academic hospitals was 19 ± 3.3 days (19, 20). An individual RCT will require 342 patients to detect a one-day increase in VFDs with a type I error (Alpha) of 0.05 and a power of 80%. According to previous studies, an intra-cluster correlation coefficient of 0.03 is used to calculate the sample size for the cluster RCT (33, 34), which results in a target of 551 recruited patients. Accounting for 15% of immeasurable PMI during PSV (19, 20), a sample of 648 will be the target, with an approximate average recruiting 40 patients in 16 participating ICUs.

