#### Primary outcome

2.6.1

The primary outcome is the ventilator-free days (VFDs) at day 28 after enrollment. The calculation of VFDs will follow the standard recommendations (30, 31).

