#### Secondary outcomes

2.6.2

Secondary outcomes include:

Duration of mechanical ventilation before enrollment;Total duration of mechanical ventilation;The time before the first SBT, which is defined as the time interval from intubation and mechanical ventilation to the first SBT attempt;Weaning time, which is defined as the time from the first SBT attempt to successful discontinuation of mechanical ventilation (28);Frequency of prolonged weaning, which is defined following WIND classification (28);Frequency of self-extubation, re-intubation, tracheotomy, and mechanical ventilation longer than 21 daysLength of stay in the ICU and hospital;ICU mortality, hospital mortality, and 28-day mortality.

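### The sample size uses an SD of 3.3 days around a mean of 19 VFDs, which allows at most 2.9% of patients to score zero, so the stated 80% power is very probably not delivered

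*Protocol article*

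**What the plan says.** Section 2.9.1 (Sample size estimation) takes its planning values from the group's earlier studies: the mean (± SD) "VFDs in Chinese academic hospitals was 19 ± 3.3 days". The aim is to "detect a one-day increase in VFDs with a type I error (Alpha) of 0.05 and a power of 80" per cent. From there:

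- "An individual RCT will require 342 patients".
- For clustering, "an intra-cluster correlation coefficient of 0.03 is used to calculate the sample size for the cluster RCT", "which results in a target of 551 recruited patients".
- After a 15% allowance for immeasurable PMI, "a sample of 648 will be the target, with an approximate average recruiting 40 patients in 16 participating ICUs".

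Section 2.6.1 (Primary outcome) makes VFDs at day 28 the primary outcome and says of scoring only that "The calculation of VFDs will follow the standard recommendations". Section 2.6.2 (Secondary outcomes) lists "ICU mortality, hospital mortality, and 28-day mortality" and ventilation beyond 21 days. Section 2.9.1 does not say whether deaths were scored zero in the 19 ± 3.3, gives no expected share of zeros, and shows no range for the SD.

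**The concern.** VFDs usually have a spike at zero, because death and failure to come off the ventilator by day 28 both score zero. With a mean of 19, each zero lies 19 days below the mean, so even a small share dominates the variance. An SD of 3.3 leaves almost no room for that spike. Yet the trial enrols ventilated patients with acute hypoxic respiratory failure and a PaO2/FiO2 of 300 mmHg or less, and plans an ARDS subgroup.

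The 342, 551 and 648 all scale with the square of the SD. If 3.3 describes survivors or a selected cohort, the one-day target at 80% power is not what 648 patients deliver. Ethics committees and later readers of the result would then be relying on a power figure that is too high.

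**Working it through.** **Inputs.** Mean 19, SD 3.3, difference 1 day, alpha 0.05 (two-sided reproduces the plan's figure), power 80%, ICC 0.03, 16 ICUs and a 15% allowance, all from Section 2.9.1. Zero for death or ventilation through day 28 is an assumption, being the usual convention. The share p scoring zero is also an assumption, shown as a range.

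**1. The plan's own figures.**
- Per arm: 2 × 3.3² × (1.96 + 0.84)² / 1² ≈ 171, so 342 in total.
- Design effect: 1 + (342/16 − 1) × 0.03 = 1.611, and 342 × 1.611 = 551.
- Allowance: 551 / 0.85 = 648.

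The figures reproduce, so the question is the SD that goes in. By the plan's own accounting, 648 recruited patients amount to 342 effective ones.

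**2. How many zeros the SD allows.** If a share p scores 0 and the overall mean is 19, the others average 19/(1 − p). Even if they are all identical, the variance is at least 19² × p/(1 − p). Setting this to at most 3.3²:

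p ≤ 3.3² / (3.3² + 19²) = 10.89 / 371.89 = 2.9%.

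Rounding of 19 and 3.3 moves the limit only between 2.7% and 3.2%. The limit is reached only if every other patient has the same value, about 19.6 days; any spread among them lowers it.

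**3. What a larger zero share does.** There are two readings, each with a test of means on the 342 effective patients. SE = SD × √(4/342), power = Φ(1/SE − 1.96), detectable difference at 80% power = 2.80 × SE.

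- Reading A: the overall mean stays at 19. Minimum SD = 19 × √(p/(1 − p)).
- Reading B: 19 ± 3.3 describes non-zero patients only. SD = √[(1 − p) × 3.3² + p(1 − p) × 19²].

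| Assumed p | A: minimum SD | A: power for 1 day | B: SD | B: power for 1 day | B: detectable difference |
|---|---|---|---|---|---|
| 5% | 4.4 | 56% | 5.2 | 42% | 1.6 days |
| 10% | 6.3 | 31% | 6.5 | 30% | 2.0 days |
| 20% | 9.5 | 16% | 8.2 | 20% | 2.5 days |
| 30% | 12.4 | 11% | 9.1 | 17% | 2.8 days |

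Example, B at 5%: 0.95 × 10.89 + 0.0475 × 361 = 27.5, SD 5.2. SE = 5.24 × 0.108 = 0.57, power = Φ(1.76 − 1.96) = 42%.

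**4. The rank test.** Section 2.9.2 assigns the Mann–Whitney test to non-normal variables, which VFDs with a spike at zero would be. A simulation of a one-day shift among non-zero patients (19 against 20, SD 3.3), with 648 patients and a design effect of 1 + (40.5 − 1) × 0.03 = 2.185, that is about 148 effective patients per arm, gives power of about 62%, 53%, 36% and 24% at 5%, 10%, 20% and 30% zeros. This uses a larger design effect than the table. At SD 3.3 with no zeros, that design effect alone takes a test of means to 74%, so not all of the shortfall here comes from the zeros.

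**The case against.** **The article proves neither premise.** Zero-scoring enters only through the cited recommendations, no event rate is given, and the cohorts behind 19 ± 3.3 cannot be inspected. This stands. A reader might infer that the 3.3 cannot include any zeros at all. The arithmetic does not say that; it says no more than 2.9%. That fewer than 3% is implausible is a judgement, though a strong one in this population.

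**The listed outcomes do not establish zeros.** A mortality outcome carries no rate. Ventilation beyond 21 days need not mean zero: with up to 7 days allowed before enrolment (Section 2.3.2), a patient ventilated for 22 days in total, 7 of them before enrolment, still has 28 − 15 = 13 VFDs. Moribund patients and those on extracorporeal support are excluded, and patients must already be on PSV with no or light sedation. This selection lowers the zero share. Nothing in the article shows that it brings it below 3%.

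**The power figures are not ceilings.** A reader might take the Reading A column as the most power the trial can have. It holds only for a test of means with the overall mean fixed at 19. At 30% zeros that requires the remaining patients to average 27.1 VFDs, hard to reconcile with an expected need for ventilation of at least 24–48 h (Section 2.3.1). Reading B gives more power at 20% and 30%, and the rank test gives more again.

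**Consequently** the stronger inference, that the trial cannot detect one day and that a null result would be uninformative, is not supported. At 5% zeros the detectable difference is about 1.6 days under Reading B, and the rank test keeps about 62% power. What remains is that every reading falls well short of 80% once 5% or more score zero.

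**Conclusion.** The concern holds as a statement about a planning input. The bound of 2.9% follows exactly from the plan's own mean and SD. That the SD probably describes survivors or a selected cohort is an inference from how low that bound is; Section 2.8 does refer to the source studies as physiologic. Given zero-scoring and a zero share of 5% or more, power for one day by a test of means on the plan's own basis is about 56% at best and falls to between 11% and 17% at 30% zeros. The rank test does better, but still runs from about 62% down to 24%. The stated 80% is therefore very probably not delivered; how far short depends on a zero share that the article does not give.

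This is not a complaint about what an article leaves out. The SD is stated, and it drives every figure in Section 2.9.1. The design effect, which uses about 21 patients per ICU rather than the planned 34 to 40, is a separate matter and is kept out of the table above.

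**What to change.** 1. Recompute the mean and SD of VFDs from the source data of the earlier studies, with deaths and patients still ventilated at day 28 scored zero, and report the share of zeros.
2. In Section 2.9.1, replace the claim of 80% power for a one-day increase with the power, or the detectable difference, for 648 patients over a stated range of zero fractions, computed for the test that will be used.
3. Optionally, check the pooled SD and ICC blind to allocation during recruitment, so that the planning figures can be corrected.

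The cost is a reanalysis of the group's own earlier data and a change of wording. No extra enrolment is asked for. The downside is a less favourable stated power.

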#### PSV setting strategy

2.4.3

In both the PMI-targeted and VT/RR-targeted groups, the same principle PSV settings are followed except for the adjustment of pressure support level:

The inspiratory trigger sensitivity is set as 1–2 L/min for the flow-trigger or 1.5–3 cmH_2_O for the pressure-trigger;Inspiration-to-expiration cycle-off is set as 25% of the peak inspiratory flow. Responsible physicians can adjust this parameter in case of suspected cycle-off patient-ventilator asynchrony;FiO_2_ and PEEP are set to maintain SpO_2_ between 90 and 95%. Specifically, if SpO_2_ is lower than 90%, PEEP and then FiO_2_ will be increased by 2 cmH_2_O and 0.1, respectively; whereas if SpO_2_ is higher than 95%, FiO_2_ and then PEEP will be decreased by 0.1 and 2 cmH_2_O, respectively.

In the VT/RR-targeted group, the pressure support is adjusted to obtain a VT between 6 and 8 mL/kg PBW, RR between 20 and 35 breaths/min, and no signs of respiratory distress, such as prominent use of the accessory respiratory muscles, nose flaring, retractions, etc. (Figure 2A).

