**Figure 2 fig2:**
[figure not shown]
Pressure support setting and adjustment strategy in VT/RR-targeted group **(A)** and PMI-targeted group **(B)**. PBW, predicted body weight; PMI, pressure muscle index; RR, respiratory rate; VT, tidal volume.

In the PMI-targeted group, the pressure support is adjusted according to the algorithm shown in Figure 2B. During PSV, after an end-inspiratory airway occlusion, Paw will reach a plateau. PMI can be measured on the ventilator screen as plateau Paw minus peak Paw by using a sliding marking line when the screen frozen function is initiated. According to our previous studies, a PMI value of 0 to 2 cmH_2_O will be used as the target for pressure support adjustment. This PMI range represents a well-accepted normal inspiratory effort (19, 20).

During the study period in the two groups, pressure support adjustment will be performed at least twice daily.

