#### Statistical analysis plan

2.9.2

All statistical analyses will be conducted in accordance with the intention-to-treat principle. That is, all randomized patients will be analyzed in the groups to which they were originally allocated. Researchers performing statistical analysis will be blinded to the cluster grouping.

Categorical variables will be presented as numbers and percentages and compared using the chi-squared test or Fisher’s exact test. For continuous variables, normal distribution will be checked by Kolmogorov–Smirnov Test, and presented as mean and standard deviation or median and interquartile range, as appropriate. Comparison of continuous variables will be performed by Student’s *t*-test for normally distributed variables and the Mann–Whitney U test for non-normally distributed variables.

Time-to-event variables will be analyzed using survival analysis, and the difference between groups will be assessed with the log-rank test.

The patients will be stratified *a priori* into subgroups with:

high versus intermediate and low respiratory drive according to the P0.1 criteria reported by a previous study (29);diagnosis of acute respiratory distress syndrome (ARDS) versus non-ARDS according to the Global definition (35);long versus short duration of controlled ventilation before enrollment according to the median obtained in all enrolled patients.

Statistical analyses will be performed using MedCalc (2022 MedCalc Software Ltd., Belgium). A *p* value of less than 0.05 is considered statistically significant.

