There are two major potential problems in the present study. The first is the accessibility of a stable plateau Paw during end-inspiratory occlusion and the measurement of PMI. This maneuver is not widely applied in clinical practice because airway occlusion may induce an unstable plateau Paw (32). However, relatively high incidences of unstable occluded Paw were reported in retrospective PMI analyses in which the main purpose was not the measurement of plateau pressure in the original studies (16, 41). In our previous study, we integrated a training and quality control approach emphasizing several key points during the end-inspiratory occlusion (check of air leak, observation of zero flow during the occlusion, and a length of occlusion longer than 2 s) (19, 20). Incidence of immeasurable plateau pressure decreased to less than 10%. These results were confirmed by a recently published study by another research group (18). Second, in our experience and results from published investigations (42), it seems that PSV is only used as a mode for preparing the liberation of mechanical ventilation in many Chinese ICUs. However, an international prospective cohort study demonstrated that the use of PSV had increased over the past two decades and became the most commonly used assisted ventilation mode during the acute phase of critical illness (2). As mentioned above, the training in standard clinical management of mechanical ventilation, especially for the initiation of PSV, will be emphasized before the start of the trial. We hope this approach might enrich our recruitment. However, because there is substantial heterogeneity in the mechanically ventilated patients, subtypes of patients may have a different response to the support pressure adjustment. For example, patients with AHRF are quite different from those with ARDS (43). Although we predefined post-hoc subgroup analysis, future work with prespecified subgroups will be needed and helpful, such as patients with abnormal low or high inspiratory drive and effort.

In conclusion, IT-PSV is a cluster RCT that will evaluate the effect of a PMI-targeted pressure support setting and adjustment strategy on the duration of mechanical ventilation in patients undergoing PSV. If positive, it will provide a new physiological-based PSV management that could potentially facilitate protective assisted ventilation.

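### The step from 551 to 648 treats immeasurable PMI as 15% loss in both arms, but the intention-to-treat analysis loses nobody; the problem is incomplete delivery in the PMI arm

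*Protocol article*

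**What the plan says.** Section 2.9.1 (Sample size estimation) starts from 342 patients for an individually randomized trial, raises this to 551 for clustering at an intra-cluster correlation of 0.03, and then takes a last step: "Accounting for 15% of immeasurable PMI during PSV (19, 20), a sample of 648 will be the target". It plans about 40 patients in each of 16 ICUs.

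Four other parts of the article bear on that step:

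- Section 2.9.2 (Statistical analysis plan) follows intention to treat: "all randomized patients will be analyzed in the groups to which they were originally allocated".
- Section 2.6.1: "The primary outcome is the ventilator-free days (VFDs) at day 28 after enrollment". This can be observed whether or not PMI is measured.
- Section 2.4.3 uses PMI in one arm only. There, "a PMI value of 0 to 2 cmH_2_O will be used as the target for pressure support adjustment". The control arm has a different target: "In the VT/RR-targeted group, the pressure support is adjusted to obtain a VT between 6 and 8 mL/kg PBW", together with respiratory rate and absence of distress.
- The exclusion criteria in Section 2.3.2 do not mention immeasurable PMI.

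The Discussion, describing the same group's work with training and quality control and citing the same two references, reports: "Incidence of immeasurable plateau pressure decreased to less than 10" percent.

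**The concern.** Dividing a total by one minus a fraction is the standard allowance for patients who contribute no outcome. Here it is applied to both arms for a measurement problem that affects treatment in only one, and under an analysis that keeps everyone. The stated reason for 648 and the stated analysis do not fit together.

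The two mechanisms have different arithmetic. Loss of patients costs a factor of 1/(1 − p) in sample size. Non-delivery to a fraction p of one arm shrinks the between-arm difference, and sample size grows with the inverse square of that difference. Depending on what the one-day effect means, the factor used is either not needed or too small.

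At stake is what 648 protects against. Taken as a drop-out allowance, the sentence could also later be cited to justify leaving unmeasured patients out. Since control patients are not titrated on PMI, that would in practice remove patients from the PMI arm only.

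**Working it through.** **Inputs.** From Section 2.9.1: SD 3.3 days, difference 1 day, alpha 0.05, power 80%, ICC 0.03, 16 ICUs, 15% immeasurable. Two-sided testing is assumed; it reproduces the stated 342.

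**The plan's own figures.**

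- Per arm: 2 × (1.960 + 0.842)² × 3.3² / 1² = 170.9, so 171 per arm and 342 in total.
- Design effect: 551 is reproduced with 342/16 = 21.375 patients per ICU. 1 + (21.375 − 1) × 0.03 = 1.611, and 342 × 1.61125 = 551.0. The article does not print 1.611; it is back-calculated.
- Last step: 551/0.85 = 648.2. The alternative 551 × 1.15 = 634 does not match. So 15% was treated as loss from the whole sample.

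**What immeasurable PMI does under the stated analysis.** Let p be the fraction of PMI-arm patients who cannot be titrated and r the share of the benefit they still receive. If one day is the effect under full delivery, the intention-to-treat difference is 1 − p(1 − r) days, and the required sample size is multiplied by 1/[1 − p(1 − r)]².

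- One day is already the intention-to-treat effect: no multiplier. 551 suffices on the protocol's own arithmetic.
- Full-delivery effect, p = 0.15, r = 0: difference 0.85 day, multiplier 1/0.85² = 1.384, and 551 × 1.384 = 763 (design effect held fixed).
- Break-even for the factor actually used, 1/0.85: this needs 1 − p(1 − r) = √0.85 = 0.922, so p(1 − r) = 0.078. At p = 0.15, r = 1 − 0.078/0.15 = 0.48. At p = 0.10, r = 1 − 0.078/0.10 = 0.22.

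Relative to 551, the plan's factor is therefore adequate if unmeasured patients keep about half the benefit at 15% immeasurable, or about a fifth at 10%, and inadequate if they keep less.

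**Power of 648 at the planned cluster size.** 648/16 = 40.5 patients per ICU.

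- Design effect: 1 + 39.5 × 0.03 = 2.185.
- Effective size: 648/2.185 = 296.6, or 148.3 per arm.
- SE = 3.3 × √(2/148.3) = 0.383.
- Power = Φ(difference/SE − 1.960).

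| PMI-arm patients gaining nothing | Difference (days) | Power of 648 |
|---|---|---|
| none | 1.00 | 74% |
| 10% | 0.90 | 65% |
| 15% | 0.85 | 60% |

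At the back-calculated 1.611 the same rows would read 86%, 78% and 73%. Those figures hold for 21.4 patients per ICU, which is not what the article plans, and should not be quoted as the power of 648. All of these use a normal approximation with equal cluster sizes and ignore the pair matching.

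**The case against.** The strongest reply is that the plan merely adds patients, which is safe, and that nothing in the article says the one-day difference applies only to patients with measurable PMI. If one day is the intention-to-treat difference, incomplete delivery is already inside it, no dilution applies, and 648 is simply larger than 551. This stands as far as it goes: the article does not say which effect is meant, so no shortfall from immeasurable PMI is demonstrated.

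Zero benefit is also an extreme case. The article states that "pressure support adjustment will be performed at least twice daily", so a failed occlusion can be repeated. Figure 2B is not shown, and the Discussion says that both algorithms provide for the target not being reached. This stands too, and it is why zero benefit is only an upper bound. A fallback rule would change the amount of dilution; it would not take anyone out of an intention-to-treat analysis.

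A reader might infer more in three ways, none supported by the article:

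- *That the trial is underpowered because of immeasurable PMI and must recruit 763.* This needs both a full-delivery effect and no benefit at all in 15% of the PMI arm.
- *That the investigators intend to exclude unmeasured patients.* The text does not say so, and Section 2.9.2 says the opposite.
- *That 15% and less than 10% contradict each other, or that 15% is a deliberate planning margin.* The cited studies are not at hand, the two rates may be defined differently, and no sentence calls the 15% a margin. Using the higher rate errs on the safe side in any case.

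**Conclusion.** The mismatch holds: 648 rests on a loss adjustment to both arms, while the stated analysis has no such loss and the difficulty lies in the PMI arm alone. This does not depend on an unseen analysis plan, because the reason for 648 and the analysis that conflicts with it are both in the article.

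The practical size is open. The right factor lies between 1 (one day is the intention-to-treat effect) and 1.384 (full-delivery effect, no benefit in 15% of the PMI arm); the plan uses 1.176. Which value applies depends on two things the article does not fix: what the one-day difference represents, and how much benefit unmeasured patients keep.

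The drop from 80% to 74% with no dilution comes from cluster size, not from immeasurable PMI. It enters here only because any restated power for 648 must use the planned 40 or so patients per ICU.

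**What to change.** Keep 648 and revise the last step of Section 2.9.1:

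- Remove the 15% loss adjustment as the basis of 648. Suggested wording: *The recruitment target is 648 patients. Patients with immeasurable PMI remain in the intention-to-treat analysis; the target allows for incomplete delivery of the strategy in the PMI-targeted group.*
- State whether the one-day difference is the intention-to-treat effect or the effect under full delivery.
- Restate the power of 648 at about 40 patients per ICU (design effect about 2.185 at ICC 0.03): about 74% with no dilution and, if one day is a full-delivery effect, about 65% or 60% when 10% or 15% of PMI-arm patients gain nothing. Do not print figures based on 1.611.
- Ask the sponsor to reconcile the 15% with the rate below 10% in the Discussion, without labelling it a margin unless the sponsor confirms that.

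The cost is a few sentences in one section. No extra patients are required by this point, and procedures, training and the case report form do not change.
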